There are numerous high-altitude regions around the world. Asia is home to the world’s highest point, Mount Everest in the Himalayas, at 8848 m above sea level (m asl). Around 400 million people worldwide live at altitudes above 1500 m asl [26,27], while around 140 million live permanently at altitudes between 2500 and 5500 m asl [28,29]. In addition, it is estimated that more than 100 million tourists visit mountainous areas around the world each year [30,31]. People’s interest in outdoor activities at high altitudes, such as hiking, mountaineering, skiing, and even following of these sports by amateurs, has increased considerably in recent years [32].

Being and moving at high altitudes produces various physiological effects, including an increase in cardiac and respiratory workload, especially during exercise [33,34]. Performing and maintaining quality CPR at high altitude could pose a significant physical challenge for rescuers. Preliminary studies have shown that, in resuscitators, after five minutes of CPR at altitude, arterial blood oxygen saturation (SaO_2_) decreases, and heart rate (HR) and the rating of perceived exertion (RPE) increase. This fact negatively affects the number of effective CCs, ultimately decreasing the quality of the CPR [27,28,29,30]. These variations have been studied by various authors at altitudes between 3100 and 3700 m asl [34,35,36,37,38,39].

Currently, it is not uncommon to find sports teams and supporters that exceed these altitudes during practice or monitoring. However, there are no studies analysing the quality of CPR performed at very high altitudes or how CPR results change after programmed conditioning at that altitude.

Normobaric intermittent hypoxia (NIH) involves breathing air with a low oxygen concentration at sea level. Its goal is to produce improvements typically associated with altitude acclimatisation, such as enhanced performance (increased oxygen transport, greater muscle efficiency and improved metabolic function), as well as haematological benefits (increased secretion of erythropoietin, haemoglobin and erythrocytes) [40]. However, haematological changes should be interpreted with caution, as it is likely that most protocols do not achieve the level of hypoxia required to induce meaningful erythropoiesis or lasting increases in haemoglobin mass [41].

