The main aim of the study is to analyse the effect of reducing the fraction of inspired oxygen (FiO_2_) at medium and high altitudes (3000 and 5000 m asl) on the quality of the basic CPR performed on adults. The secondary objectives are (a) to assess the perception of effort and levels of anxiety involved in performing CPR at these altitudes; (b) to determine whether there is an association between altitude, body mass index (BMI) and physical fitness and the proportion of correct CCs achieved at the proposed altitudes; (c) to analyse the muscle oxygen saturation (SmO_2_) values during CPR at the proposed altitudes; (d) to determine the blood variations produced (lactate, haematocrit (Hct), haemoglobin (Hgb), creatine phosphokinase (CPK), and myoglobin (Mb)); and (e) to assess the quality of the CPR components (CCs and ventilations), the ratings of perceived exertion (RPE), and associations between BMI, SmO_2_ and anxiety levels at 670, 3000 and 5000 m asl after an adaptation programme to intermittent hypoxia.

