### 2.4. Interventions

#### Training CPR Programme

Participants without prior CPR training will undergo a standardised training programme designed in accordance with current European Resuscitation Council (ERC) guidelines. The training programme will consist of: (1) a theoretical session (60 min), including basic life support principles, recognition of cardiac arrest, and CPR sequence; (2) a practical hands-on training session (120 min), during which participants will practice chest compressions and ventilations using feedback-enabled mannequins under instructor supervision; and (3) a supervised skill consolidation session (30 min) focused on correcting technique and ensuring adherence to guideline criteria (compression depth, rate, recoil, and ventilation quality). The total training duration will therefore be approximately 3.5 h. Training will be delivered by certified instructors following a structured protocol to ensure standardisation across participants. Objective feedback devices will be used to facilitate motor skill acquisition and improve CPR quality performance. This training duration is consistent with previous literature demonstrating that structured sessions of at least 2–4 h are required for adequate acquisition of basic CPR skills and retention of performance quality.

Stage 1: An initial baseline assessment will be carried out in all participants (*n* = 56), consisting of collection of parentage data and anamnesis, as well as the measurement of physiological variables at rest (resting electrocardiogram and pulmonary function test), which will allow ruling out the existence of pathologies that contraindicate the performance of ergospirometry. Other measurements include diastolic blood pressure (DBP) and systolic blood pressure (SPB), anthropometry, ergospirometry to determine the maximal HR achieved and VO_2_max, muscle strength, and initial hypoxia tolerance test.

Stage 2: All participants (*n* = 56) will perform 10 uninterrupted minutes of CPR (with a CC/ventilation ratio of 30:2) on a mannequin with a quality measurement device for CTE and ventilations (Q-CPR) in the following situations:

Test M1: CPR at 670 m asl, FiO_2_ of 0.21.

Test M2: CPR at normal pressure simulating 3000 m asl, FiO_2_ of 0.14.

Test M3: CPR at normal pressure simulating 5000 m asl, FiO_2_ of 0.11.

Prior to M2 and M3, each participant will have an acclimatisation period of 10 min to FiO_2_ corresponding to each of the altitudes.

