To minimise the effect of fatigue between tests, each participant will have a 24 h rest period.

Stage 3: Participants assigned to the intervention group will undergo a standardised intermittent hypoxia conditioning programme (13 sessions, 45–75 min/session), including alternating cycles of hypoxia (FiO_2_ progressively reduced from 0.14 to 0.11) and normoxia, resulting in a total hypoxic exposure of approximately 728 min. The control group will undergo a sham protocol consisting of identical session structure and duration under normoxic conditions. Three to five weekly sessions will be held according to tolerance and the iAltitude^®^ protocol [42].

Stage 4: After the intervention, all the participants (*n* = 56) will perform three uninterrupted 10 min sessions of CPR: the first at 670 (P1), the second (P2) at 3000, and the third (P3) at 5000 m asl. To minimise the effect of fatigue between tests, each participant will have a 24 h rest period [42]. The criteria for completing the different CPR tests will be determined by reaching 10 min or by the physical and/or physiological limitations of the rescuer (physical exhaustion or pain, SatO_2_ < 75).

Throughout all stages, heart rate and peripheral oxygen saturation (SpO_2_) will be continuously monitored using an ear clip pulse oximeter. The training programme instructs the participant to breathe ambient air if the SpO2 level exceeds the limit specified in Table 1 (Lim SpO2). During hypoxia tests, as well as during conditioning, a nurse and/or a doctor with experience in emergency care will be present.

To minimise potential confounding due to independent practice, participants will be explicitly instructed not to perform any additional CPR training or practice outside the study protocol during the study period.

The pre-conditioning protocol for high-altitude exposure was designed based on experience and knowledge regarding the use of normobaric intermittent hypoxia (IHT) to enhance sporting performance. To this end, the following data were collected from each participant: age, sex, height, weight, body fat percentage, sport practised (if applicable), number of weekly training sessions, time spent training, and ability to perform CPR manoeuvres in accordance with the study design.

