### 2.6. Statistical Analysis

First, a descriptive analysis of the study variables will be carried out, along with the appropriate tabulation and graphical representation of the data. Qualitative variables will be expressed as proportions with 95% confidence intervals, and quantitative variables will be described using means and standard deviations or medians and interquartile ranges, as appropriate. Prior to the application of parametric tests, the assumption of normality will be assessed for all continuous variables using the Shapiro–Wilk test.

For comparisons involving paired quantitative data, Student’s *t*-test for paired samples will be used when the normality assumption is met. If this assumption is violated, the non-parametric Wilcoxon signed-rank test will be applied.

For between-group comparisons (intervention vs. control), independent-sample t-tests will be used for normally distributed variables, while the Mann–Whitney U test will be used for non-normally distributed variables.

To evaluate the effect of the intervention across time and altitude conditions, a mixed-model ANOVA will be used, including group (intervention vs. control) as a between-subject factor and time (pre vs. post) and altitude as within-subject factors.

For categorical variables, McNemar or chi-square tests will be applied as appropriate.

A multivariate linear regression analysis will be performed to adjust for potential confounding variables (age, sex, BMI, and physical fitness), including group allocation as an independent variable. Model assumptions (normality, homoscedasticity, and independence of residuals) will be checked.

Statistical significance will be set at *p* < 0.05. All statistical analyses will be performed using IBM^®^ SPSS^®^ Statistics 28 software.

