## 3. Discussion

The results of this study will have the practical utility of demonstrating that CPR, even though it is a submaximal effort manoeuvre, is subject to being performed by anyone without motor disabilities regardless of the environment in which it is performed. Our study will also provide evidence as to whether this characteristic continues to hold true in a hostile environment such as medium and high altitudes.

Our study aims to demonstrate that improvement in physical performance and recovery capacity induced by intermittent hypoxia conditioning programmes increases the quality of CPR in prolonged cardiac arrests and in adverse conditions, such as at high altitudes.

In the same way, information will be given about how often the exchange of resuscitators is recommended to avoid errors in CPR manoeuvres as a result of rescuer fatigue under such adverse conditions.

The proposed study will contribute as a novelty to the estimation of the influence of high altitudes and conditioning on performing basic CPR manoeuvres.

If the hypothesis turns out to be true, recommendations about the practice of moderate-intensity physical exercise could be incorporated into the CPR guidelines as one of the important aspects in the training of rescuers to face CPR.

Limitations of this study include the fact that CPR will be performed not on a patient, but on a mannequin. However, a better performance under “real” conditions would have been more likely to occur since chest compressions are easier to perform on human beings. Similarly, simulating high altitude by reducing FiO_2_ in the laboratory eliminates other factors associated with high altitude, such as ambient temperature and reduced O_2_ pressure, the time of year of assessment, geographical conditions, the type and quality of food and the presence of unhealthy habits. On the other hand, the laboratory environment is very different from what usually surrounds sudden cardiac arrest in the community setting, and rescuers might vary their response when a sense of urgency appears.

A second limitation could be the effect that real-time audio-visual feedback during CPR manoeuvres has on the performance of the study participants, which may limit the generalisability of our findings to situations where this feedback procedure is not used.

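### In a laboratory at 670 m, FiO2 0.14 simulates about 3630–3810 m, not the 3000 m on the label

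*Protocol article*

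**What the plan says.** The Introduction states the main aim, with CPR quality as the outcome, as follows: "to analyse the effect of reducing the fraction of inspired oxygen (FiO_2_) at medium and high altitudes (3000 and 5000 m asl"). Section 2.4, Stage 2, sets three conditions. The reference is room air: "Test M1: CPR at 670 m asl, FiO_2_ of 0.21". The middle one is "Test M2: CPR at normal pressure simulating 3000 m asl, FiO_2_ of 0.14". The third, M3, uses FiO2 0.11 for a stated 5000 m, also at normal pressure. Stage 4 repeats the altitudes after conditioning, "the first at 670 (P1), the second (P2) at 3000, and the third (P3) at 5000 m asl", without giving the gas settings again.

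Section 2 names a single site, and the Discussion describes the method as lowering FiO2 in the laboratory. No pressure chamber is described. The analysis (2.6) uses a mixed-model ANOVA "including group (intervention vs. control) as a between-subject factor and time (pre vs. post) and altitude as within-subject factors".

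**The concern.** The oxygen stimulus depends on inspired oxygen pressure, which is FiO2 multiplied by barometric pressure less water vapour. The same FiO2 is therefore a stronger stimulus in a laboratory at 670 m than in one at sea level. The protocol calls room air 670 m, so its labels are real altitudes above sea level and the laboratory is at 670 m. On that scale FiO2 0.14 appears too low for 3000 m.

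What is at stake is the altitude attached to the main-aim result. The Introduction says of earlier work on rescuers that "These variations have been studied by various authors at altitudes between 3100 and 3700 m asl". Taken at face value, the 3000 m label puts M2 just below that range, whereas the calculated exposure lies at its top or just above it. A fall in CPR quality reported at 3000 m would then be read as occurring lower than the altitudes already studied, when it came from hypoxia typical of that range or stronger.

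**Working it through.** **Inputs from the protocol (2.4, Stage 2).** Laboratory altitude 670 m (M1, room air); FiO2 0.14 labelled 3000 m (M2); FiO2 0.11 labelled 5000 m (M3).

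**Assumptions, not in the protocol.** Two conditions are equivalent if humidified inspired oxygen pressure is equal. Water vapour is 47 mmHg and the ambient oxygen fraction is 0.2093. Barometric pressure PB comes from one of two models:

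- Standard atmosphere: PB(h) = 760(1 − 2.25577×10⁻⁵h)^5.25588, h in metres.
- Second model: PB(k) = exp(6.63268 − 0.1112k − 0.00149k²), k in kilometres.

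| PB, mmHg | 0 m | 670 m | 3000 m | 5000 m |
|---|---|---|---|---|
| Standard | 760.0 | 701.5 | 525.9 | 405.2 |
| Second | 759.5 | 704.5 | 536.8 | 419.7 |

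**Step 1: can the 3000 m label be reproduced?** Solve 0.2093 × (PB(h) − 47) = FiO2 × (PB_lab − 47) for h. With a sea-level laboratory, FiO2 0.14 gives 3029 m (standard) or 3207 m (second), close to the label. With the laboratory at 670 m it does not:

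- Standard: M2 = 0.14 × (701.5 − 47) = 91.6 mmHg, equivalent to **3634 m**. A true 3000 m is 0.2093 × (525.9 − 47) = 100.2 mmHg.
- Second: M2 = 0.14 × (704.5 − 47) = 92.1 mmHg, equivalent to **3806 m**. A true 3000 m is 0.2093 × (536.8 − 47) = 102.5 mmHg.

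The label is low by 634 m or 806 m.

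**Step 2: can rounding, humidity or weather explain it?**

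| Variant at 670 m | Standard | Second |
|---|---|---|
| FiO2 0.145 | 3388 m | 3546 m |
| FiO2 0.135 | 3887 m | 4073 m |
| FiO2 0.14, no water vapour | 3886 m | 4070 m |
| FiO2 0.14, PB +10 mmHg | 3528 m | 3694 m |
| FiO2 0.14, PB −10 mmHg | 3741 m | 3919 m |
| FiO2 0.145 and PB +10 mmHg | 3280 m | 3433 m |

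None returns 3000 m. For FiO2 0.14 to mean 3000 m, laboratory pressure would have to be 100.2/0.14 + 47 = 763 mmHg (standard) or 102.5/0.14 + 47 = 779 mmHg (second). That is sea-level pressure or higher, against about 702–705 mmHg at 670 m.

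**Step 3: size of the stimulus.** Fall in inspired oxygen pressure from M1, taking room air as 0.2093:

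- Standard: 137.0 − 91.6 = 45.4 mmHg, against 137.0 − 100.2 = 36.8 mmHg for a true 3000 m, so 23% larger.
- Second: about 45.6 mmHg (137.6 less 92.1, before rounding), against 137.6 − 102.5 = 35.1 mmHg, so 30% larger.
- If the delivered FiO2 were 0.145, the falls are 42.1 and 42.3 mmHg, so 14% and 20% larger.

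**Step 4: FiO2 that would simulate 3000 m at this site.** 100.2/654.5 = 0.153 (standard); 102.5/657.5 = 0.156 (second).

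**Step 5: M3 for comparison.** FiO2 0.11 gives 72.0 mmHg and 5266 m (standard), or 72.3 mmHg and 5526 m (second). At FiO2 0.115 these become 4973 m and 5218 m, so under the standard atmosphere the 5000 m label is within rounding.

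**The case against.** The strongest reply is that the labels follow a sea-level convention. The Introduction says that "Normobaric intermittent hypoxia (NIH) involves breathing air with a low oxygen concentration at sea level". With FiO2 rounding allowed, a sea-level base gives 2777–3288 m (standard) or 2941–3480 m (second) for M2, and 4400–5009 m or 4650–5292 m for M3, so both labels fit. This may be how they arose, but the document does not say so. It also leaves the offset in place. On a sea-level scale room air would be 0 m, yet M1 is labelled 670 m, so one altitude factor would mix two reference scales. The sentence in the Introduction is a general definition of the method and does not describe this site.

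Second, the exposure is not hidden: FiO2 and site altitude are both stated, and no planned estimate or test is affected. That stands. Altitude is a factor with no per-metre slope, and both groups do the same tests.

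Third, the comparison with earlier studies is only a face-value reading, because the Introduction does not say whether their altitudes were real or simulated. The protocol itself claims no novelty at 3000 m. That stands too.

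Fourth, the exact offset depends on imported pressure models that differ by 172 m (3806 − 3634). Rounding and a high-pressure day together could reduce the equivalent to 3280 m, leaving 280 m unexplained. The direction holds throughout.

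Finally, the Discussion acknowledges that "simulating high altitude by reducing FiO_2_ in the laboratory eliminates other factors associated with high altitude", and lists reduced oxygen pressure among them. It does not mention that the simulated altitude is offset by the height of the laboratory.

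**Conclusion.** The concern holds. As written, M2 delivers hypoxia equivalent to about 3630–3810 m, so the 3000 m label is low by about 630–810 m. FiO2 rounding alone leaves at least 390–550 m unexplained, and the full range over FiO2 0.135–0.145 is 3388–4073 m. The result rests on the laboratory being at 670 m, which the protocol states, and on equal humidified inspired oxygen pressure with one of two assumed pressure models. Leaving out water vapour widens the gap.

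The point extends to P2 only if P2 repeats M2's gas, which Stage 4 does not state. The 5000 m label is a weaker case. The planned comparisons remain valid; the correction concerns the altitude at which a main-aim result is reported. It should be fixed.

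**What to change.** **Preferred: keep the gas and correct the label.** Record laboratory barometric pressure at each test. Report M2/P2 and M3/P3 by inspired oxygen pressure, FiO2 × (PB − 47), and by the equivalent altitude derived from it (about 3600–3800 m for M2, and for P2 if the gas is the same) in the objectives, tables and conclusions. State the FiO2 used in P1–P3. The cost is one barometer reading per test and less round altitude figures.

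**Alternative, only if testing has not begun and the device allows it.** Set FiO2 to about 0.153–0.156 in both M2 and P2, so that the condition does simulate 3000 m. This makes the test milder, and a fall in CPR quality there may be harder to detect. The change must be made in both tests or the pre/post comparison breaks.

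Neither option needs extra participants or visits.

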As indicated in the text and illustrated in Figure 2, the study protocol comprises four stages. The first stage involves performing a hypoxia tolerance test. The second stage involves carrying out CPR tests without hypoxia conditioning at different altitudes. The third stage consists of 15 sessions of IHT conditioning. Finally, the fourth stage involves performing CPR tests at the specified altitudes.

The Hypoxic Training Index (HTI) and the Hypoxic Recovery Index (HRI) are monitored in both phase 1 and phase 3. The HTI is a measure of the cumulative hypoxic stress experienced during a session and over successive sessions of the protocol. This index is calculated as an integral value of SPO2 readings below 90%. The HRI is used as an indicator of the individual’s recovery capacity following hypoxic stress during a session, and cumulatively across subsequent sessions of the protocol. It is calculated during periods when SPO2 readings are above 90%, and its value increases more rapidly the better an individual recovers from the hypoxic load to which the individual is exposed. The HTI is calculated as the area under the curve (AUC) of SpO_2_ values below 90%, expressed as %·min, representing the cumulative magnitude and duration of hypoxic stress. The HRI is calculated as the area above 90% SpO_2_ during recovery periods (also expressed as %·min), reflecting the extent and rate of reoxygenation.

In order to complete the designed IHT pre-conditioning protocol, participants will need to complete the 15 sessions detailed in Table 1. These sessions will be conducted under the supervision of a trained supervisor who will be responsible for ensuring that: (1) throughout all sessions, participants are monitored via pulse oximetry and follow the instructions provided by the iAltitude software (Hypoxiahome Trainer 4.1) at all times in order to ensure safety and achieve the expected results; (2) a minimum interval of at least 24 h is maintained between sessions, with no more than 72 h elapsing between them; (3) more than 2 h have elapsed between the participant’s last meal and the start of the session; and (4) the breathing pattern during the sessions remains natural. The breathing rate should not be increased, and the breaths should not be deep, so that the amount of oxygen inhaled corresponds to the level required for the session, based on the specified FiO_2_ percentage.

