**Figure 2 jfmk-11-00253-f002:**
[figure not shown]
Pre-conditioning protocol. FiO_2_: fraction of inspired oxygen.

**Table 1 jfmk-11-00253-t001:** Description of normobaric hypoxia training sessions.

Session Number	FiO_2_	Lim SpO_2_	Total Cycle Time (min)	Hypoxia Cycle Duration (min) [Number of Hypoxia Cycles]	Normoxia Cycle Duration (min) [Number of Normoxia Cycles]	Total Hypoxia Time (min)	Total Normoxia Time (min)
1	14	85	56	4 [7]	4 [7]	28	28
2	14	85	64	5 [8]	3 [8]	40	24
3	14	85	63	6 [7]	3 [7]	42	21
4	13	82	64	5 [8]	3 [8]	40	24
5	13	82	70	7 [7]	3 [7]	49	21
6	13	82	63	7 [7]	2 [7]	49	14
7	12	80	64	6 [8]	2 [8]	48	16
8	12	80	70	7 [7]	3 [7]	49	21
9	12	80	60	8 [6]	2 [6]	48	12
10	13	82	72	16 [4]	2 [4]	64	8
11	11	78	63	7 [7]	2 [7]	49	14
12	11	78	60	8 [6]	2 [6]	48	12
13	11	78	60	9 [6]	1 [6]	54	6

FiO_2_: fraction of inspired oxygen; Lim SpO_2_: arterial blood oxygen saturation limit.

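### The conditioning programme is given as 13 sessions, as 15 sessions and as about 728 min of hypoxia, while Table 1 lists 13 sessions totalling 608 min

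*Protocol article*

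**What the plan says.** All statements are in the protocol article.

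- Section 2.4, Stage 3, assigns the intervention group to a "standardised intermittent hypoxia conditioning programme (13 sessions, 45–75 min/session" and, in the same sentence, describes the programme as "resulting in a total hypoxic exposure of approximately 728 min".
- Section 2.4, in the paragraph that summarises the four stages: "The third stage consists of 15 sessions of IHT conditioning".
- Section 2.4, in the paragraph on supervision, as the condition for finishing the programme: "participants will need to complete the 15 sessions detailed in Table 1".
- Table 1 ("Description of normobaric hypoxia training sessions") has rows numbered 1 to 13 without a gap. Each row gives FiO2, the SpO2 limit, the cycle structure, and the hypoxia and normoxia minutes. It has no total row.
- Section 2.4, Stage 3, on the comparator: "The control group will undergo a sham protocol consisting of identical session structure and duration under normoxic conditions".

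**The concern.** The programme is what distinguishes the two randomised arms, so its session count and planned exposure define what the trial tests. The article gives two session counts, and a total exposure that its own table does not yield.

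Three things follow.

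- **Sham arm.** It copies the structure and duration of the active programme, so its length is as open as the active arm's.
- **Completion.** A participant who does every session in Table 1 has finished the programme under Stage 3, but not under the sentence that requires 15 sessions.
- **Session settings.** Section 2.4 relies on the SpO2 limit set for each session to tell the participant to remove the mask and recover. Those limits are printed only in Table 1. If 15 sessions are meant, two have no printed limit, FiO2 or cycle structure.

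**Working it through.** **Inputs.** From Stage 3: 13 sessions, 45–75 min each, about 728 min of hypoxia, three to five sessions a week. From the later paragraphs of Section 2.4: 15 sessions. From Table 1: the 13 rows.

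**Step 1. Is Table 1 legible and self-consistent?** In each row I checked that cycle duration × number of cycles equals the stated hypoxia and normoxia times, and that hypoxia + normoxia equals total cycle time. All 13 rows pass; session 10, for example, gives 16 × 4 = 64, 2 × 4 = 8 and 64 + 8 = 72. A misread cell would break these identities. Session lengths run from 56 to 72 min, which agrees with the 45–75 min in Stage 3.

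**Step 2. Can 728 be reproduced from the table?**

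Hypoxia: 28 + 40 + 42 + 40 + 49 + 49 + 48 + 49 + 48 + 64 + 49 + 48 + 54 = **608 min**

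Normoxia: 28 + 24 + 21 + 24 + 21 + 14 + 16 + 21 + 12 + 8 + 14 + 12 + 6 = 221 min

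Total: 608 + 221 = 829 min

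No column gives 728.

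**Step 3. Size of the gap.** 728 − 608 = 120 min, and 728 / 608 = 1.197, an excess of about 20%. Per session, 728 / 13 = 56.0 min of hypoxia is needed, whereas the table's mean is 608 / 13 = 46.8 min. Only session 10 (64 min) reaches 56 min.

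**Step 4. Does the other session count explain it?**

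| Possible source of 728 | Calculation | Result (min) |
|---|---|---|
| Table mean carried to 15 sessions | 608 × 15 / 13 | 702 |
| Two unlisted sessions at the table's extremes (28 and 64 min of hypoxia) | 608 + 2 × 28 to 608 + 2 × 64 | 664 to 736 |
| Two unlisted sessions averaging 60 min of hypoxia | 608 + 2 × 60 | 728 |
| 13 sessions × total cycle time of session 1 | 13 × 56 | 728 |

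The last two rows both give 728 exactly, for unrelated reasons. The article supports neither, so the arithmetic cannot identify the source of the figure.

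**Step 5. What the session count changes.** At three to five sessions a week, 13 sessions take 13/5 = 2.6 to 13/3 = 4.3 weeks, and 15 take 3 to 5 weeks. Time in session, in either arm, is 829 min for the 13 printed sessions. If two more were added, and assuming that each fell within the table's 56–72 min, it would be 829 + 112 = 941 to 829 + 144 = 973 min.

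**The case against.** The best defence is that little of the inference rests on these figures. They do not enter the sample size calculation (Section 2.3), the Q-CC outcome (Section 2.5) or the mixed-model ANOVA (Section 2.6). The rule for the sham arm is relative, so the arms stay matched whichever count applies, provided both use the same one. Sessions 1 to 13 are fully specified and could be run as printed. Exposure is also followed in each participant through the Hypoxic Training Index, and a participant who crosses the SpO2 limit returns to ambient air. Both 608 and 728 min are therefore planned figures, not delivered ones.

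All of this stands, and it limits the consequences. It does not remove the conflict. A matched sham arm still needs a stated length, individual monitoring does not say how many sessions are planned, and the word approximately does not cover a 20% excess. Figure 2 is not shown, but it could not reconcile text sentences that disagree with each other. Lost table rows are unlikely, because the numbering is unbroken and Stage 3 also says 13.

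A reader might infer more than the documents support:

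- **That Table 1 is right and the text wrong.** Row consistency shows that the printed rows are not garbled. It cannot show that the list is complete or current.
- **That 728 is left over from a 15-session version.** Step 4 shows a second route that fits equally well.
- **That any dose reported in the results would be wrong.** Delivered exposure is monitored individually and can be reported as such.

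**Conclusion.** The contradiction is real: 13 against 15 sessions, and 728 against 608 min of planned hypoxia, a difference of 120 min or about 20%. It rests only on figures printed in the article and on Table 1 being reproduced faithfully, which the row checks and the unbroken numbering support. The documents do not show which figure is wrong.

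The effect is on the definition, uniform delivery and reproducibility of the randomised intervention, on the length of its sham counterpart, and on what counts as completing the programme. The validity of the randomised comparison is not in question as long as both arms follow one list. The point still needs correcting before conditioning starts, because the article does not fix what is to be delivered.

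**What to change.** Before the first conditioning session, the investigators should:

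1. Reconcile Stage 3, the two later statements of the session count in Section 2.4, and Table 1 to one session list. Which list is theirs to decide.
2. Print that list in full, with every session's settings, so that no planned session lacks FiO2, cycle structure or SpO2 limit.
3. Restate the planned hypoxic exposure as the sum of the final list, ideally in a total row in Table 1, and label it as planned so that it is not confused with delivered exposure.
4. Use the same session count for the sham arm and for the completion requirement.

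The cost is a text and table correction. It adds no procedures and does not touch the sample size or the analysis model.
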